## Abstract

Background: There is a global agreement in the medical community that a significant proportion of dementia cases could be prevented or postponed. One of the factors behind this agreement comes from scientific evidence showing that mind-body interventions such as mindfulness and yoga for the elderly have been related to a range of positive outcomes, including improved cognition performance in seniors with mild cognitive impairment (MCI). Objective: This study aims to evaluate the effectiveness of a yoga-based mindfulness intervention (YBM) versus psychoeducational sessions for older adults with MCI attending Hospital Clinic Universidad de Chile in Santiago. Method: Two-arm, individually randomized controlled trial (RCT) will be carried out at Clinical Hospital Universidad de Chile in Santiago. Older people over 60 years with any type of MCI using a score < 21 in the Montreal Cognitive Assessment (MoCA) test and a score of 0.05 in the Clinical Dementia Rating (CDR) Scale; and with preserved activities of daily living will be randomly assigned with an allocation ratio of 1:1 in either the yoga-based mindfulness intervention or the active control group based on the psycho-educational program. People who have performed yoga and/or mindfulness in the last 6 months or/and people with a psychiatric clinical diagnosis will be excluded from the study. Montreal Cognitive Assessment, the Lawton Instrumental Activities of Daily Living Scale (IADL), the Barthel Index (BI), the Pemberton happiness index, the Geriatric Anxiety Inventory (GAI) as well as the Geriatric Depression Scale (GDS-5) will be administered by blinded outcomes assessors before random assignment (Pre-test), the week following the last session of the intervention (post-test), and then after 3- and 6-months follow-up. Results: The YBM intervention protocol based on a video recording has been adapted and designed. This is the first RCT to examine the effects of a yoga-based mindfulness intervention in improving cognitive and physical functions and mental health outcomes for Chilean elderly diagnosed with MCI. It is expected to be implemented as an acceptable and effective non-pharmacological option for older people with MCI. Conclusion: Providing evidence-based programs such as preventive therapy for Alzheimer’s disease has relevant implications for public mental health services in Chile.

## 1. Background

Demographers and social scientists have noted that a transition toward an older global population has been underway in many parts of the world. In October 2022, new projections from the World Health Organization (WHO) revealed that by 2050 the proportion of the global population who are over 60 years old would increase from 12% to 22% [1]. By that time, the proportion of people over 65 years old will rise to 16 percent of the global population, compared to 10 percent in 2022 [2], which confirms the demographic transition toward a more elderly global population [3]. This has not only been occurring in developed countries such as Japan, The European Union, and The United States, but it has also been occurring in developing countries as well. By the year 2090, the Latin American and the Caribbean region is expected to have the highest percentage of people aged over 60, at around 36 percent of the total regional population [3]. It is estimated that the number of Chileans over 60 years old will increase from the current 15.7% of the population to 32.9% by 2050 [4], and the proportion of people older than 80 will reach 10.3% [5].

Along with this shift towards a more aged population, there has been a greater incidence of illnesses and disorders that are more commonly associated with this group. One of these is dementia, a progressive decline of the cognitive ability which predominantly affects people over the age of 60. It has emerged as a main public health concern [6]. It is projected that the number of people in the world with dementia will reach 131.5 million by 2050 [7]. This disorder has become more prevalent in every country where the elderly population has increased. Chile is one of these countries where dementia has become a significant cause of disability among the elderly, with a prevalence of 10.4% (10.6% women, men 10.1%) [8]. The need for preventive treatment is particularly evident if we consider that WHO estimates that there will be a 77% increase in the cases of dementia by 2030 in Chile, Argentina, and Uruguay [9].

Dementia is usually preceded by a phase called mild cognitive impairment (MCI), a stage between the normal cognitive changes caused by aging and early dementia [10]. It encompasses a wide range of cognitive impairments such as memory, executive function, attention, language, or visuospatial skills [11]. Ample evidence has emerged that MCI has become equally prevalent among this segment of the population. A 2016–2017 National Health Survey reported that 10% of adults over 60 years old had suspected MCI, reaching 21% in those over 80 [12]. In the global sample, the prevalence of MCI for ages 60 to 64 years old was 6.7% [13]. However, in adults over 65 years, the prevalence increases to 14.8% and reaches 25.2% in those over 80 [13]. A number of studies have provided evidence that people with MCI are at greater risk of developing Alzheimer’s disease (AD) [14]; 5–15% of people with MCI are diagnosed with AD each year [15].

In addition, the elderly often experience depression and anxiety, which are common in people with MCI [16]. Recent findings indicate that people with MCI have a greater risk of developing the depressive disorder and anxiety disorder [17]. Previous studies show that the proportion of people with MCI who have depressive symptoms ranges between 36% to 63% [18]. Anxiety symptoms are equally frequent, with rates between 10 and 74% [16]. Chileans over 65 diagnosed for the first time with depression presented a greater link with cognitive impairment [19]. Other studies have also shown that depression and anxiety are risk factors for MCI [10,20] and that these conditions often precede the development of AD [21].

The decline in cognitive ability causes difficulty for older people in executing their daily activities [22] and has been associated with declines in functional status, quality of life, and increased dependency as well as mortality [23]. Albala [24] points out that the loss of physiological functioning because of aging reduces the resistance to stressors, leading to the greater vulnerability of older adults and to the development of frailty syndrome [24]. Frailty is strongly associated with cognitive impairment and depression in older Chilean adults [24].

Physical and mental health have been found to be related to subjective well-being. Many older adults experience lower levels of well-being due to such decline in their physical and cognitive functions [25] as well as social losses and chronic conditions, limiting their activities and leading to depression and anxiety [26]. Therefore, new interventions are needed to address multiple aspects of well-being in the elderly, helping them to maintain good health and to lead independent lives.

These data and facts highlight the importance of offering adequate care to the elderly population through treatments that bring about improvements in their cognitive and physical function. However, after numerous clinical trials, there are still no effective drugs approved by the Food and Drug Administration (FDA) for the treatment of MCI [27] or for postponing the progression to dementia [28].

Therefore, non-pharmacological therapies based on mind-body exercises, such as yoga and mindfulness, have been found to be feasible and effective intervention options for older adults with MCI [29,30,31,32].

Yoga is an ancient mind-body practice rooted in India whose main emphasis is to arrive at the “here and now” by using physical postures (asanas), breath control (pranayama), and meditation (dyana) [33]. Yoga has been known to boost physical and psychological well-being [34,35,36,37,38], reduce depression and anxiety [38], as well as to delay frailty in older adults [39]. Yoga-related interventions for the elderly are safe, practical, and acceptable practices for the strengthening of cognitive functions of those suffering age-related cognitive deterioration [40]. Findings of a study conducted by Tremont et al. [41] point out that the yoga intervention was safe, feasible, and effective for elderly patients with MCI. The authors obtained preliminary proof that yoga can ameliorate visuospatial functioning in MCI patients [41]. The results of the same study considered a reduction in stress as a potential mechanism for the yoga intervention [41]. Several major studies have demonstrated that cognitively impaired older adults could benefit from cognitive improvement through yoga intervention. In a study conducted by Chobe et al. [42], yoga intervention significantly improved global cognition as well as other cognitive abilities, including learning, attention, processing speed, and working memory among elderly persons with MCI.

Furthermore, an earlier study conducted by Gothe and McAuley [43] showed some beneficial effects of Hatha yoga on cognitive functions, including attention and processing speed, as well as executive function and memory [44]. In another study, the results showed that yoga, breathing exercises, and the practice of mindfulness meditation boosted brain wave activity as well as amygdala and frontal cortex activation in older people [45]. Moreover, yoga intervention demonstrated statistically significant development in the executive function of elderly patients with MCI as compared to memory enhancement training (MET) and a larger effect on depressive symptoms and resilience [30]. A previous study also confirmed that kundalini yoga is associated with improved neural activity and brain structural alterations associated with executive function [46], as well as improved memory performance, awareness, and attention in seniors with MCI [47].

Mindfulness therapy involves developing awareness of the present moment in a non-judgmental manner. A common type of intervention based on this therapy is called Mindfulness-based stress reduction (MBSR), which teaches mindfulness meditation and yoga [48]. MBSR may be categorized in terms of formal activities such as body scanning, breath meditation, loving-kindness meditation, and yoga and informal practices such as awareness in daily routines like mindful eating, walking, and communicating [49].

Due to its potential to reduce the main risk factors of dementia in late life, including depression, anxiety, and stress, accompanied by sleep disorders, mindfulness therapy has been found as a practical and efficacious intervention for strengthening the cognitive function of people with MCI and delaying the progress of MCI to AD [29,32,50]. Numerous studies indicate that such training can be an effective alternative treatment. Initial findings by Larouche et al. [51] showed that mindfulness-based intervention could prevent memory loss and can improve mood and quality of life in people with MCI. Findings of a recent pilot feasibility study in MCI patients indicated that MBSR is a potentially promising intervention with beneficial effects on cognition, psychological health, and the immune system [52]. In a study conducted by Fam et al. (2020), elderly with MCI who practiced mindfulness had better brain network efficiency and neuro-cognitive function rather than the control group. In this study, the author suggested that mindfulness may be of benefit to the older adult population with early stages of cognitive deterioration.

A further study conducted by Kinjal et al. [53] found that elderly with MCI receiving eight weeks of mindfulness-based training presented significant improvements in global cognition, with significant developments in delayed memory than participants in the cognitive rehabilitation therapy group. The results of a recent review indicated that such interventions improved cognitive function, motor control, and mindfulness, resulting in a reasonable reduction in the risk of falling, a decrease in symptoms of depression and stress, and a lower risk of dementia in adults with MCI [29]. A meta-analysis also suggests that mind-body training such as yoga and mindfulness positively impact attention, working memory, executive function, and global cognition [54]. However, inconsistent results of other meta-analyses conducted by Han [55] found no significant effect of mindfulness-based interventions on psychological outcomes, memory, and overall cognitive functions compared to comparison groups.

The results of a randomized, controlled pilot clinical trial showed that MCI participants in MBSR had increased functional connectivity within the default mode network (DMN), along with reduced hippocampal atrophy as compared to the usual care group [56]. Different findings suggest that mindfulness could arrest the cognitive decline in MCI as well as prevent the pathological symptoms of AD, namely progressive loss in the hippocampus and grey matter, along with decreased functional connectivity in the DMN [56,57,58].

The results of a study by Wong et al. [32] showed that cognitive function and mindfulness levels were enhanced after finishing a mindfulness intervention program. It also revealed that older adults with MCI who meditated for more than the average amount of time between program completion and one-year follow-up showed more significant gains in their cognitive and daily functioning [32].

Based on the evidence, applying an appropriate body-mind intervention for older people is effective in improving cognitive function, functional independence, and mental health outcomes, thereby delaying frailty and improving well-being in this population. However, comparatively few randomized, controlled trials (RCTs) interventions have been done, mainly in elderly patients with mild MCI, who are at increased risk of developing dementia. Furthermore, Chile’s epidemiological profile, characterized by the tendency towards a growing proportion of elderly adults with an increased incidence of dementia and mental illnesses, has prompted the search for an effective non-pharmacological intervention incorporating a mind-body component to improve cognitive and physical functions as well as mental health outcome. In addition, there have been no studies to demonstrate the effects of a yoga-based mindfulness intervention on cognitive decline in the elderly with MCI in Chile. Clearly, evidence from Chile and other countries in Latin America is needed. To address this, a study of early intervention using a yoga-based mindfulness component to prevent dementia in Chile is hereby proposed. Hence, a yoga-based mindfulness component would be utilized to design the intervention.

General Objective: To compare the effectiveness of yoga-based mindfulness (YBM) intervention versus psycho-educational sessions (PES) in improving cognitive and physical functions and mental health outcomes for older adults with mild cognitive impairment (MCI).

Specific Objectives:(1)To compare the change in cognitive function scores between older adults with MCI receiving a YBM intervention versus those receiving a PES intervention.(2)To compare the change in physical function scores between older adults with MCI receiving a YBM intervention versus those receiving a PES intervention.(3)To compare the change in well-being scores between older adults with MCI receiving a YBM intervention versus those receiving a PES intervention.(4)To compare the change in anxiety and depression scores between older adults with MCI receiving a YBM intervention versus those receiving a PES intervention.(5)To assess the correlation between cognitive function and physical function in older adults with MCI, controlling for psychological variables (depression, anxiety, well-being), and group (YBM intervention or participating in PES)

**Hypothesis 1.** *Older adults with MCI in the YBM intervention will have a different change in their cognitive function—as measured through MoCA assessment, before and after the intervention—than those in the PES intervention (with the same measures, before and after)*.

**Hypothesis 1.1.** *Older adults with MCI in the YBM intervention will have a different change in their physical function—as measured through the Barthel Index (BI) and The Lawton Instrumental Activities of Daily Living Scale (IADL) before and after the intervention—than those in the PES intervention (with same measures, before and after)*.

**Hypothesis 1.2.** *Older adults with MCI in the YBM intervention will have a different change in their well-being—as measured through the Pemberton happiness index, before and after the intervention—than those in the PES intervention (with the same measures, before and after)*.

**Hypothesis 1.3.** *Older adults with MCI in the YBM intervention will have will have lower anxiety and depression levels—as measured through the Geriatric Anxiety Inventory (GAI) and the Geriatric Depression Scale (GDS-5), before and after the intervention—than those in the PES intervention (with same measures, before and after)*.

**Hypothesis 2.** *Cognitive function will have an effect on physical function in older people with MCI, mediated by psychological factors (depression, anxiety, and well-being)*.

## 2. Method

### 2.1. Trial Design

This is a two-arm, individually randomized controlled trial, superiority with an allocation ratio of 1:1, assessor-blinded, and 3- and 6-months follow-up. This study protocol has followed the SPIRIT guidelines [59]. Trial registration: A protocol for this study has been registered retrospectively at the ISRCTN registry on 28 April 2022. Identifier: ISRCTN13063260. https://www.isrctn.com/ISRCTN13063260, accessed on 28 April 2022. An overview is presented in Figure 1.

### 2.2. Study Setting

Participants will be recruited at Universidad de Chile Clinical Hospital in Santiago, Chile.

### 2.3. Participants

The target population corresponds to people aged 60 years and more with any type of MCI, and the eligibility criteria for the selection of the sample consisted of the following:Having 60 years and above,People who have MCI are diagnosed by three criteria:
➢by a neurologist and/or psychiatrist, and/or geriatrician, and/or neuropsychologist. through evaluation by saying that they had memory problems confirmed by an informant (in case they have a formal or informal caregiver or simply, their partner), (but without problems in their activities of daily living);➢and with a score < 21 on the Montreal Cognitive Assessment (MoCA < 21).
Without dementia, according to the criteria of the Clinical Dementia Rating Scale (CDR), a score of 0.05.

The Exclusion criteria would be:People who performed yoga and/or mindfulness within the last 6 monthsThe presence of a psychiatric clinical diagnosis; or neurological/cerebrovascular condition.Presence of a disabling physical illness or/and presence of a disability that limits and/or impede communication, such as major impairments in eyesight, and/ hearing or upper limb motor movements, and/or other health problem that would interfere with regular yoga and mindfulness practice.

Attendants to the secondary care center (clinical hospital Universidad de Chile) who meet these criteria will be invited to participate in the study and will be randomized to an experiment or control group.

### 2.4. Recruitment and Informed Consent Process

Within the clinical hospital Universidad de Chile, users 60 years old and above that are receiving care at the clinic will be invited to participate in the study and will be referred by secondary care professionals (Physicians derived from health networks can be informed post-randomization). Prior to inclusion in the study, a psychiatrist, neurologist, or geriatrician will determine the patient’s capacity to consent to participate in the study before considering his/her inclusion. Therefore, qualified recruiters from the trial will contact potential participants (e.g., MoCA < 21) for evaluation of the initial eligibility criteria for the study, and before starting the evaluation process, overall characteristics of the trial will be explained to participants, and verbal informed consent will be obtained from them during the recruitment phone call. Participants who meet the inclusion criteria and agree to participate will be evaluated through a trained evaluator, with a battery of evaluation instruments using a telephone-based survey, and then they will be randomized to either the intervention or control group. Outcome assessments will also be conducted through these evaluators, blinded to the allocation of the intervention. However due to the nature of the psychosocial intervention, it will not be possible to blind the MCI participant. The secondary care team will be informed regarding MCI patients’ assignments after randomization.

To ensure a sufficient recruitment flow, recruiters will work on a daily basis in the morning under the supervision of the person in charge, who will be in close contact with the research team. To facilitate the work of the recruiters and to invite potential participants to contact them, leaflets and banners with basic information about the study will be available at the clinical hospital Universidad de Chile. Recruiters will also be in direct contact with neurologists or psychiatrists about each potential participant.

### 2.5. Randomization

The outpatient clinic within Clinical Hospital at Universidad de Chile will be allocated to the intervention or the comparator with a 1:1 ratio based on the random computer-generated numbers, using simple random sampling by sequentially numbered. In order to generate a random allocation sequence, a balanced block randomization will be used with a randomly varying block size of 4. A member of the research team who is not involved in the recruitment process in the outpatient clinic will oversee the generation of the random sequence and the allocation of the interventions. Allocation will be kept concealed from the recruiters by hiding the process from executive personnel of the Clinical Hospital, who will be obviously instructed not to contact health care staff at the participating centers. Randomization will be carried out once the initial evaluation has been carried out for all participants, avoiding the bias that could occur when randomization during the recruitment process.

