### 2.6. Sample Size

The sample size is estimated based on changing the primary outcome (MoCA) according to the MCID/MCIC (Minimal Clinically Important Difference or Change), which has been established in a study performed by Wong et al. [60]. This Study suggested that a change of 2.0 can be considered as a reasonable minimum, clinically important difference for the main outcome variable (MoCA). Therefore, based on the previous study [32] examining mindfulness’s effect on the cognitive function of seniors with MCI, we estimated the effect size to be 0.5. Hence, we required 18 participants for each arm to have a power of 80% to detect statistical significance at a 5% level which was determined based on an analysis performed in the data of Wong et al. [32] using the Stata 17. Considering potentially a drop-out rate of 20%, 22 participants will be required to be allocated to each group. Therefore, the targeted total sample size will be 44 in order to sustain enough power in the present study.

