## 6. Analysis

Descriptive analyses of relevant variables will be conducted for the total sample and for each group separately in order to assess the balance between the intervention group and the control group after randomization, thus, for categorical variables, the percentage and frequency will be presented for each intervention group, and for continuous variables, means and standard deviations for each intervention group, along with the mean difference between the groups, 95% CI, and *p* value will be presented. In order to determine if there are significant differences in pre and post-evaluation between groups, a mixed design analysis of the variance model with repeated measures (ANOVA) will be performed. One factor, between-subject factor, would consider a “group” (composed of older MCI in the YBM intervention group and older MCI in the active control group with PSE), and the other factor, repeated measures or within subjects’ factor, would be considered as “time” (composed by “pre”, “post”, & “follow up” measures) for primary and secondary outcomes.

In order to report the strength of the YBM intervention, the effect size will be calculated as well, level of significance will be set at *p* < 0.05 with 95% CI, Therefore, based on the repeated measure Anova, effect size calculation would be performed using the standardized mean difference (SMD), Cohen’s d [77]. According to the main outcomes of the study and the condition of the intervention program, since educational level, age and sex are considered as potential confounders o covariates, so they will be controlled at baseline in the Ancova model, and it will enter to model as factor or covariance using the continuous measure. Hence, effect size calculation would be performed using Partial Eta^2^. Moreover, subgroup analyses will be performed to test the possible mediator as well. All the analyses will be based on the intention-to-treat principle, accounting for loss-to-follow-ups, and will be performed using Stata, version 17.0.

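### Baseline MoCA is known for the whole sample before allocation, but neither the unstratified blocks nor the ANCOVA as described makes use of it

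*Protocol article*

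**What the plan says.** Protocol article, section 2.5 (Randomization): "Randomization will be carried out once the initial evaluation has been carried out for all participants", with the stated purpose of "avoiding the bias that could occur when randomization during the recruitment process". For the list itself, "a balanced block randomization will be used with a randomly varying block size of 4". No stratification, minimisation or matching factor is named. Section 2.1 gives "superiority with an allocation ratio of 1:1".

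Table 1 places MoCA and demographics at enrolment, before allocation. It places the other scales (BI, IADL, PHI, GAI, GDS-5) at t1, under the post-allocation heading, although section 4 puts the pre-test before random assignment.

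Section 2.6 gives the yardstick: "a change of 2.0 can be considered as a reasonable minimum, clinically important difference". The target is 22 per arm, 44 in total.

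Section 6 plans a mixed ANOVA with group and time, where the pre score is one level of time. It then describes an ANCOVA, "since educational level, age and sex are considered as potential confounders o covariates". Baseline MoCA is not in that list.

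**The concern.** Waiting until everyone has been evaluated has one statistical benefit: the list can be arranged to balance the arms on the baseline value of the primary outcome. The plan accepts the wait but does not take the benefit. Blocks of four on a numbered list equalise the arm counts and nothing else.

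In a trial of 44 people a visible chance gap in baseline MoCA is quite possible. The group-by-time contrast is in effect a comparison of changes. It does not remove the part of a baseline gap that is due to regression toward the mean. A baseline MoCA covariate would do so, but the ANCOVA does not name one. At stake are some precision and an avoidable argument about imbalance when the result is reported.

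**Working it through.** **Inputs from the protocol article.** 22 per arm and a minimal important difference of 2.0 points, so half of it is 1.0 (section 2.6); 1:1 blocks of four, so 44/4 = 11 complete blocks (section 2.5); entry MoCA below 21 (section 2.3).

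**Input not given: the SD of baseline MoCA.** Section 2.6 does not settle it.
- It states "we estimated the effect size to be 0.5" and "we required 18 participants for each arm to have a power of 80% to detect statistical significance at a 5% level". Read as a standardised mean difference, 0.5 needs 63 per arm (two-sided 5%, 80% power), and 18 per arm gives 31-32% power. The stated 18 is therefore not reproduced.
- Dividing 2.0 by 0.5 would imply an SD of 4.0, whereas 2.0 points with 18 per arm would imply an SD of about 2.1.
- The section confirms neither reading. The sample-size discrepancy is a separate matter. Here it means only that the SD has to be assumed.
- Simulated integer scores capped at 20 had SDs of about 1.7 to 2.9, so 1.9 to 3 is used as the working range.

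**Step 1: chance of a gap with the planned blocks.** The arm difference in baseline MoCA is approximately normal with mean 0 and SD = s × √(2/22). The chance of a gap of 1.0 or more in either direction is 2 × [1 − Φ(1 / (s × √(2/22)))].

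| Assumed s | SD of arm difference | Chance of gap ≥ 1.0 |
|---|---|---|
| 1.9 | 0.57 | 8% |
| 2.0 | 0.60 | 9.7% |
| 2.5 | 0.75 | 18.5% |
| 3.0 | 0.90 | 26.9% |
| 4.0 (2.0/0.5) | 1.21 | 41% |

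Simulating 11 permuted blocks of four with truncated integer scores agrees: for example 8.6% at a realised SD of 1.87, 15.3% at 2.24 and 22.0% at 2.61.

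**Step 2: how much of a gap reaches the estimate.** Let g be the baseline gap and b the slope of post on pre. Given g, the expected post gap is the true effect plus b × g. The change contrast subtracts g, so it equals the true effect minus (1 − b) × g. With g = 1.0 the shift is 0.4 points at b = 0.6 and 0.2 points at b = 0.8 (b is assumed). That is 10% to 20% of the 2.0-point difference.

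**Step 3: what the remedies do to the gap.** These are simulated with normal scores, 6,000 runs per SD.

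| Assumed s | Blocks on MoCA-ordered list | Two strata split at the median |
|---|---|---|
| 2.0 | 0% (SD of gap 0.13) | 0.5% |
| 2.6 | 0% (0.16) | 3.7% |
| 3.0 | 0% (0.19) | 7.0% |

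**Step 4: where the precision comes from.** With equal pre and post variances the slope equals the correlation r. The variance of the change contrast is proportional to 2(1 − r) and that of the baseline-adjusted contrast to 1 − r². The ratio is (1 + r)/2, which is 0.80 at r = 0.6 and 0.90 at r = 0.8. Adjustment alone therefore saves 10% to 20% of the variance. Once adjusted, chance imbalance in one covariate inflates the variance by (44 − 3)/(44 − 4) = 41/40, or 2.5%. Balancing in advance spares at most about that much.

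**The case against.** The strongest reply is that nothing here is wrong. Unstratified permuted blocks are a standard, valid method, and chance imbalance is already reflected in the standard error and the p value. The group-by-time model uses the pre score, so a baseline gap reaches the estimate only in part. Most of the gain comes from a model term, which concerns section 6 more than section 2.5. All of that stands, and it makes this an efficiency point.

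The premise can also be questioned. Section 2.4 has participants evaluated and then randomised, which could mean each person after his or her own evaluation. The purpose stated in section 2.5, to avoid randomising during recruitment, fits batch allocation better, but the two passages are not fully aligned. If allocation is person by person, an ordered list is impossible and only strata remain. Nor can all baseline data be called known beforehand, since Table 1 puts the other scales after allocation. The claim is safe for MoCA and demographics.

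Finally, section 6.1 mentions a full protocol. If that document stratifies on MoCA, the part about the list falls away.

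**Conclusion.** The point holds as a missed and nearly free gain in precision. On section 2.5's wording, baseline MoCA is known for the whole sample, the list ignores it, and the ANCOVA does not name it. For assumed baseline SDs of about 1.9 to 3, a gap of 1.0 point or more has a chance of roughly 8% to 27%, and a 1.0-point gap shifts the change contrast by 0.2 to 0.4 points if the slope is 0.6 to 0.8.

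A reader might infer more than this, and the documents do not support it:
- That the allocation is biased or invalid. It is neither.
- That the chance is one fixed figure, such as one in five. That needs an SD of about 2.6, which appears nowhere in the article.
- That chance gaps rival the effect sought. A gap of 2.0 points has a chance of only about 0.05% at an SD of 1.9 and 2.7% at an SD of 3, and even then only part of it would reach the estimate.
- That the remedy balances education, age and sex as well. Ordering or stratifying on MoCA balances MoCA only.

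**What to change.** **Section 6 (the larger gain).** Add baseline MoCA as a covariate in the primary outcome model, beside education, age and sex. The cleanest form takes the pre score out of the time factor, so that baseline is not both outcome and covariate.

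**Section 2.5.** State that the block list is applied to participants ordered by baseline MoCA, with a stated rule for ties. Alternatively, use blocks within two MoCA strata. Strata reduce the gap less than ordering does, but they are the option if allocation is person by person; the cut point must then be set in advance. With strata, the model should carry at least the stratum. Sections 2.4 and 2.5 should say plainly which timing applies.

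**Cost.** One sentence and one model term, with no further data, staff or participants. The change to the list must be made before allocation. If allocation has already been done, the model term can still be added before outcome data are examined. The one downside is that the model must carry the MoCA term once the list is balanced on it, otherwise the confidence intervals are too wide.
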